## Abstract

**Introduction:**

Myeloma, a blood cancer originating from plasma cells, is the most common indication for autologous stem cell transplantation (SCT). Patients with myeloma undergoing autologous SCT (ASCT) experience treatment-related morbidity and reduction in function and well-being for many months post-treatment. Interventions targeting physical functioning delivered prior to and during SCT have shown promising results in mixed haematological populations and may offer a non-pharmacological solution to physically optimising and preparing patients for SCT. The aim of this study is to investigate the feasibility of a physiotherapist-led exercise intervention as an integral part of the myeloma ASCT pathway at a UK tertiary centre.

**Methods and analysis:**

PERCEPT is a single-site, pilot randomised controlled trial of an exercise intervention embedded within the myeloma ASCT pathway, compared with usual care. The primary study end points will be feasibility measures of study and intervention delivery including recruitment rates, acceptability of intervention, study completion rate and any adverse events. Secondary end points will evaluate differences between the exercise intervention group and the usual care control group in cancer-related fatigue, quality of life, functional capacity (6 min walk test; handheld dynamometry; a timed sit-to-stand test) and objective and self-reported physical activity. Outcomes will be assessed at four time points, approximately 6–8 weeks prior to SCT, on/around day of SCT, on discharge from SCT hospital admission and 12 weeks post-discharge. The exercise intervention comprises of partly supervised physiotherapist-led aerobic and resistance exercise including behaviour change techniques to promote change in exercise behaviour. The primary outcomes from the trial will be summarised as percentages or mean values with 95% CIs. Group differences for secondary outcomes at each time point will be analysed using appropriate statistical models.

**Ethics and dissemination:**

This study has NHS REC approval (Camden and Kings Cross, 19/LO/0204). Results will be disseminated through publication and presentations at haematology and rehabilitation-related meetings.

**Trial registration number:**

ISRCTN15875290.

Strengths and limitations of this studyThis study features a pragmatic trial design integrated into the existing autologous transplant treatment pathway and the use of a partly supervised exercise intervention, which will incorporate behaviour change techniques (BCTs), in myeloma patients before, during and after stem cell transplantation.It is the first study of a prehabilitation and rehabilitation exercise intervention in myeloma transplant recipients in the UK to incorporate a control arm.Although the intervention includes exercise and incorporated BCTs, it does not include nutritional assessment and/or dietary intervention, as recommended in guidance for prehabilitation interventions.This study is a single-site pilot trial and is not statistically powered.

## Introduction

Myeloma, also known as multiple myeloma, is an incurable blood cancer of plasma cells in the bone marrow and accounts for 10% of all haematological cancers.^1 2^ The incidence is approximately 22 cases per 100 000 people in the UK.^1^ Although incurable, improved understanding of disease mechanisms and advances in treatments means that survival in myeloma is increasing at the fastest rate among all cancer types.^3^ Median-estimated survival time for myeloma has quadrupled over the last four decades and 5-year survival is now around 47%.^4^

Myeloma patients are treated with autologous stem cell transplantation (SCT) if eligible (based on age and performance status).^5^ Autologous SCT (ASCT) involves harvesting the individual’s own stem cells and re-infusing them after high-dose chemotherapy.^6^ ASCT has been shown in multiple randomised controlled trials (RCTs) to prolong progression-free survival, and in some studies overall survival in myeloma.^2 7^ In the UK, the total numbers of ASCTs carried out each year have been increasing by 5% each year.^8^ Data from the British Society of Blood and Marrow Transplant register shows that myeloma is the most common indication for ASCT in the UK, with 1411 procedures taking place in 2016.^9^ However ASCT has a number of side effects,^5^ including repeated infections, nausea, anorexia and fatigue and patients can suffer a reduction in their functionality and well-being for 6 to 12 months post-transplantation.^10^ There is a need to develop supportive interventions for patients undergoing ASCT aimed at optimising patient fitness before and during ASCT in order to mitigate or minimise the negative effects of treatment on physical and psychological outcomes.^11^ Prehabilitation and rehabilitation, targeting physical function and fitness, have been suggested as an integral component of myeloma treatment pathways in guidance for managing the consequences of the disease and its treatment; however, further research is required to better understand the potential impact of prehabilitation/rehabilitation before and after treatment for myeloma.^12^ Given the prevalence of myeloma-related bone destruction in this population, it is also vital to develop and test tailored exercise interventions that are safe and effective at enhancing physical capacity in the presence of disease-related skeletal deformity and pain, common symptoms that limit patients with myeloma being physically active during and after treatment.^13^

There is emerging evidence that exercise during or after SCT may be beneficial. However, existing studies have generally been small, with methodological limitations, particularly the heterogeneity of the interventions and mixed haematological cancer populations studied.^14 15^ Two systematic reviews, of 8 and 11 RCTs, respectively, have shown that exercise is safe and feasible for people being treated for different types of blood cancer during hospital admission and that the best results are seen when exercise is introduced before or during treatment, when compared with usual care. The majority of the studies included in these reviews were carried out with patients undergoing allogeneic SCT or mixed samples of both allogeneic SCT and ASCT recipients using varied interventions.^16 17^ There is acknowledged variation in symptoms and consequences of treatment experienced by patients with different bloods cancers, and between undergoing allogeneic SCT and ASCT.^16 18^ Studies among allogeneic SCT recipients highlight the intensive nature of the medical intervention and its associated symptom burden and consequences, most notably graft versus host disease (GvHD) and an increased risk of treatment-associated mortality.^19^ In contrast, with autologous transplantation the mortality is considerably lower and there is no risk of GvHD, with its attendant risk of infections and short-term and long-term morbidity.^18^ These variations in clinical features support the need to study rehabilitation interventions in uniform blood cancer patient populations.

Only two small trials have explored the use of a pre-transplant exercise in a myeloma only population undergoing ASCT, with mixed results.^20–22^ In the first study, a feasibility study of 24 participants showed a significant increase in lean muscle mass in the exercise group.^20^ The second study of 166 patients reported a decline in aerobic capacity and increased fatigue in both the experimental and control group, with no difference between groups after SCT. This study, reported in two papers, was also testing the effect of prophylactic epotin alfa therapy, a medical product that raises haemoglobin levels, alongside exercise and was therefore not solely assessing the efficacy of the prescribed exercise.^21 22^ Additional limitations to these studies include provision of an unsupervised home-based exercise intervention and that the control groups were also advised to walk 20 min/ day,^20 21^ which may have diluted the effect size. These studies, however, have demonstrated that it is safe for myeloma patients to exercise while undergoing ASCT.

Limited published literature exists regarding physical activity (PA) or exercise interventions in patients undergoing SCT originating in the UK. A single-arm pilot study of a physiotherapist-led, tailored, exercise intervention delivered to myeloma survivors post-treatment conducted at the authors’ centre demonstrated that exercise was associated with improvements in quality of life (QOL), cancer-related fatigue and muscle strength, and it was extremely well received by patients.^23^ A single-arm study to test feasibility of delivering exercise during ASCT among people with myeloma in a centre in Sheffield has completed recruitment but the results are yet to be published.^24^

### Objectives

This primary aim of this pilot, single-centre, RCT is to investigate the feasibility of a physiotherapist-led exercise intervention as an integral part of the ASCT pathway for patients with myeloma. It is hypothesised that this intervention, delivered before and during ASCT treatment for myeloma, will be feasible in terms of recruitment rate and willingness of the participants to be randomised, intervention adherence, compliance to the exercise prescription and attrition due to the intervention.

Primary objectives of the pilot study are to measure eligibility and recruitment rates from potential participants screened on referral to myeloma outpatient clinics for consideration for ASCT; acceptability of the intervention, including adherence to exercise sessions and deviations from exercise protocol; study completion rate and any adverse events.

Secondary objectives are to collect preliminary data on the intended primary/secondary outcomes of a future fully powered RCT to obtain mean and SD estimates to inform a sample size calculation. These outcomes include: cancer-related fatigue; QOL; levels of PA and sedentary time; functional capacity and muscle strength; hospital length of stay, rates of readmission and health service utilisation and if the trial/exercise intervention is delivered as intended.

Exploratory objectives are to investigate any effect on immune parameters (including immunoglobulins, T cells, B cells, natural killer cells).

## Methods and analysis

### Participants

All patients with a diagnosis of myeloma referred to University College London Hospitals NHS Foundation Trust (UCLH) for consideration for ASCT will be identified through discussion with the clinical multidisciplinary team (MDT) responsible for coordinating treatment for patients with myeloma, and the team includes the medical team and clinical nurse specialists (CNSs), nurses who act in a key working role to provide support for patients undergoing cancer treatment.^25^

### Inclusion and exclusion criteria

Potential participants will be screened using the inclusion/exclusion criteria by the research team and through discussion with the haematology consultants, CNSs and MDT. All adult patients with myeloma referred to UCLH for consideration of ASCT, who are clinically able to carry out an exercise training programme on a regular basis and willing and able to provide written informed consent will be deemed eligible to approach. Patients must have a good command of written and spoken English.

Patients will be excluded if they have known spinal instability, spinal cord compression or neurological deficits, have had recent (within 6 weeks) spinal surgery or other surgery for pathological fractures, have an abnormal resting ECG and/or unstable angina. Patients will also be excluded if they are unable or unwilling to undertake an exercise programme on a regular basis or are unable or unwilling to provide informed consent.

The initial aims of this study were developed with input from participants in myeloma survivorship research conducted at our centre. The study has been further developed through involvement of the UCLH Cancer Patient and Public Advisory Group (CPPAG) during the preparation of the grant application and development of the study protocol. The CPPAG will continue to be provided with updates on the progress of the study and its results.

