### Recruitment procedures

A participant information sheet (PIS) detailing the study will be provided in a clinical information pack routinely posted to patients prior to their first routine transplant clinic appointment. Potential participants will be contacted by the principle researcher or study physiotherapist, with a follow-up telephone call to allow patients to ask questions about the study. Those who wish to proceed will be asked to provide informed consent and this will be recorded on the participant consent form. Those approached to take part in the study who are subsequently found to be ineligible or decline to take part will be recorded in a screening log by the principle investigator.

It is conservatively estimated that approximately 60–75 patients will be recruited over a 15–18-month period, with completion of final follow-ups within 18–21 months. Approximately 100 myeloma patients undergo ASCT at UCLH each year.

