### Outcome assessment

The primary end points of this pilot study will be study feasibility. A target recruitment rate of >50% of potential participants screened as eligible and approached for this study will be a primary indication of feasibility. Feasibility of delivering the intervention protocol will be assessed by evaluating adherence to the intervention and acceptability of receiving the intervention (including deviations from exercise protocol). Attrition due to the intervention, loss to follow-up and adverse events will also be assessed.

A number of secondary end points will also evaluate any between group differences and determine intended primary and secondary end points for a fully powered trial. Fatigue will be assessed using the Functional Assessment of Chronic Illness Therapy (FACIT-F) questionnaire.^35^ QOL will be measured with two complementary instruments: the European Organisation for Research and Treatment of Cancer QOL Questionnaire (EORTC QLQ-C30 and myeloma-specific module QLQMY20)^36 37^ and the Functional Assessment of Cancer Therapy Bone Marrow Transplantation (FACT-BMT) scale questionnaire.^38^ The EORTC QLQ C-30 has a focus on physical and functioning dimensions of QOL whereas FACT-BMT can assess impact of treatment and side effects on QOL. Comparison analysis indicates that both instruments should be used together rather than in place of each other when assessing QOL in patients undergoing SCT.^39 40^

Functional capacity will be assessed with a 6 min walk test (6MWT), handheld dynamometry and a timed sit-to-stand test. PA and sedentary time will be recorded over 5–7 days using an ActivPAL accelerometer (PAL Technologies, Glasgow, UK). Additional measures of self-reported PA behaviour will be captured using the self-complete short form International Physical Activity Questionnaire^41^ and the Exercise Self-Efficacy Scale.^42^ All these measures will be recorded at baseline and three time points during the ASCT pathway. At the final time point, an adapted Client Service Receipt Inventory questionnaire will be used to assess health and social care usage in the time following hospital discharge.^43^

The outcomes measures and time points for data collection are summarised in table 2.

**Table 2 T2:** Study schedule of assessments

Visit no.	Screening	Baseline assessment (T0)	Follow-up 1 (T1)	Follow-up 2 (T2)	Follow-up 3 (T3)
		1	2	3	4

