	On referral to UCLH ASCT MDT	On day of first transplant clinic appointment	Day of transplant	Day of discharge from hospital	Post-transplant follow-up clinic at 3 months
Qualitative interview (~20 patients who decline study)	X				
Window of flexibility for timing of visits		±2 days	0±1 day	0±1 day	±5 days
Screening eligibility	X				
Informed consent		X			
Demographics and clinical history		X			
Fatigue: FACT-F		X	X	X	X
QOL: EORTC QLQ C-30-MY20		X	X	X	X
QOL: FACT-BMT		X	X	X	X
Exercise behaviour: IPAQ-SF		X	X	X	X
Exercise Self-efficacy Scale		X	X	X	X
Functional capacity: 6MWT		X	X	X	X
Functional capacity: 30 s STS		X	X	X	X
Functional capacity: handheld dynamometry		X	X	X	X
Resting BP and HR		X	X	X	X
Height and weight		X	X	X	X
Accelerometery (3–7 days)		X	X	X	X
Qualitative interview (20 participants)					X
Health and social care service use: CRSI					X
Blood counts		X	X	X	X
Levels of immune function (blood)		X	X	X	X

ASCT, autologous stem cell transplant; BP, blood pressure; EORTC QLQ C-30-MY20, European Organisation for Research and Treatment of Cancer QOL Questionnaire and myeloma specific module; CRSI, Client Service Receipt Inventory; FACT-BMT, Functional Assessment of Cancer Therapy Bone Marrow Transplantation; FACT-F, Functional Assessment of Chronic Illness Therapy Fatigue questionnaire; HR, heart rate; IPAQ-SF, International Physical Activity Questionnaire short form; MDT, multidisciplinary team; 6MWT, 6 min walk test; QOL, quality of life; STS, sit to stand; UCLH, University College London Hospitals NHS Foundation Trust.

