### Qualitative data

Semi-structured interviews will be conducted with a purposeful sample of participants at two time points. Study ‘decliners’, deemed eligible for the study, who have received a study PIS but declined to enrol in the study will be asked if they would participate in a short interview. These interviews will take place either face to face in the clinic setting or via telephone (based on participants’ preference) and will be conducted to explore the patients’ experiences of being approached for the exercise study and the process and outcome of their decision-making process in relation to the exercise study.

Additional semi-structured interviews from approximately 20 participants who enrol and take part in the study will take place at final follow-up, approximately 3 months post-transplant, and will be conducted to explore the participants experiences of ASCT treatment and their experiences of being enrolled in the study. Participants will be purposively sampled to include participants from both the intervention arm and the control arm.

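### The denominator of the >50% recruitment target is contradictory: a patient who refuses because they do not want to exercise can be counted either as an eligible decliner or as ineligible.

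*Protocol article*

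**What the plan says.** All references are to the protocol article.

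- **Outcome assessment** sets the target: "A target recruitment rate of >50% of potential participants screened as eligible and approached for this study will be a primary indication of feasibility". Data analysis names the recruitment rate as a primary outcome, to be reported with a 95% CI.
- **Inclusion and exclusion criteria** makes willingness part of eligibility. Patients who meet the other inclusion conditions and are "willing and able to provide written informed consent will be deemed eligible to approach". Among those excluded are patients "unable or unwilling to undertake an exercise programme on a regular basis or are unable or unwilling to provide informed consent".
- **Recruitment procedures** posts the information sheet before the first transplant clinic visit and follows it with a telephone call. Approached patients who are "subsequently found to be ineligible or decline to take part will be recorded in a screening log".
- **Qualitative data** describes the decliners to be interviewed as "deemed eligible for the study, who have received a study PIS but declined to enrol in the study". The schedule of assessments plans about "20 patients who decline study" for interview.
- **Objectives** lists as a primary objective to "measure eligibility and recruitment rates from potential participants screened on referral to myeloma outpatient clinics".

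**The concern.** The denominator depends on the word eligible, and the article uses that word in two ways. Under the eligibility section, a patient who will not consent, or will not exercise regularly, is excluded. Under the recruitment and qualitative sections, a patient who declines was eligible and said no. One refusal cannot be both, and the two uses give different values of a primary outcome.

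The overlap is sharpest for the refusal that tells an exercise trial most: not wanting to do the exercise programme. That is the refusal the eligibility section labels an exclusion. It will usually come to light after the information sheet and the telephone call, which is also when the recruitment section allows ineligibility to be discovered.

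The >50% figure is the only feasibility threshold with a number, the Objectives section hypothesises feasibility in terms of recruitment rate and willingness to be randomised, and the Discussion links a later multicentre trial to the feasibility criteria being met. A rate that rests on an unstated coding choice is a weak basis for that step.

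**Working it through.** The >50% target is a chosen figure, not one derived from other inputs, so there is no plan calculation to reproduce. The check is how far the rate moves with the classification of refusals.

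**Context from the article.** Recruitment procedures expects that "approximately 60–75 patients will be recruited over a 15–18-month period" and gives about 100 transplants a year at the centre.

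- Pool: 100 × 15/12 = 125 patients; 100 × 18/12 = 150 patients.
- Expected recruits as a share of the pool: 60/150 = 40%, 60/125 = 48%, 75/150 = 50%, 75/125 = 60%.

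These are shares of transplanted patients, not of patients eligible and approached, so they are only a rough guide. They do straddle 50%, so a modest change in the denominator could decide whether the target is met.

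**Direction.** With r recruited, n clinically eligible patients approached and k refusals recoded as ineligible, the rate goes from r/n to r/(n − k). For k > 0 this is always larger.

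**Illustration (assumed counts).** n = 150, r = 60, so 90 refusals.

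- All refusals kept: 60/150 = 40% (Wilson 95% CI 33% to 48%).
- 40 refusals recoded: 60/(150 − 40) = 60/110 = 55% (45% to 64%).

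**Range.** Let c be the true consent share among clinically eligible patients approached, and f the share of refusals logged as ineligible. Then

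observed rate = c / [c + (1 − c)(1 − f)].

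The article gives neither c nor f; both are assumptions.

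| True consent c | f = 0 | f = 0.25 | f = 0.50 | f = 0.75 | f needed to reach 50% |
|---|---|---|---|---|---|
| 20% | 20% | 25% | 33% | 50% | 75% |
| 30% | 30% | 36% | 46% | 63% | 57% |
| 40% | 40% | 47% | 57% | 73% | 33% |
| 45% | 45% | 52% | 62% | 77% | 18% |

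The last column is 1 − c/(1 − c); for c = 0.40 it is 1 − 0.40/0.60 = 0.33. At f = 1 the rate is 100% for any c.

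**With refusals kept (f = 0).** Binomial probability of observing more than 50%:

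| Approached | c = 40% | c = 45% | c = 50% | c = 55% | c = 60% |
|---|---|---|---|---|---|
| 120 (at least 61 recruited) | 1% | 12% | 46% | 84% | 98% |
| 150 (at least 76 recruited) | 0.5% | 10% | 47% | 88% | 99% |

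With refusals kept, the target can be missed and it separates low from high consent.

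**The case against.** The strongest reply is that the article, read as a whole, keeps refusals in. The schedule of assessments places screening at referral, before consent, and the eligibility text itself speaks of being eligible to be approached. A patient who refuses after the posted sheet and the call has therefore already been screened as eligible and approached. The log names ineligible and declining patients separately, and interviews with about 20 eligible decliners are planned. If every refuser were ineligible, the rate would always be 100% and there would be nobody to interview. Wording about willingness to consent is also routine in eligibility lists.

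Most of this stands, and it rules out the stronger inference that a reader might draw from the exclusions alone: that all refusals leave the denominator and the target can hardly fail. That holds only if the exclusions are applied fully literally, against the recruitment and qualitative sections.

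It does not settle the overlap. The recruitment section lets ineligibility be found after approach, so a patient unwilling to exercise can still be logged under either heading. Naming two categories does not say which one takes that patient.

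Three further replies have partial force. First, the eligibility rate is also to be reported, so a shift of refusers into the ineligible group might show there; that would not correct the recruitment rate. Second, the target is one indication of feasibility among several and carries no formal stop/go rule, so meeting or missing it is not by itself a decision; and the decliner interviews and the log will give some information on willingness whatever the coding. Third, an article may leave log-coding detail to a full protocol. Here, though, the point is a conflict between definitions that the article does state.

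**Conclusion.** The point holds as an internal contradiction in the denominator of a primary outcome. The eligibility section counts unwillingness as ineligibility; the recruitment and qualitative sections count it as declining. Any recoding of refusals as ineligible biases the rate upward, never downward. At an assumed true consent of 40%, recoding one third of refusals brings the rate to 50%; at 45%, 18% is enough. The article does not show that such recoding will happen, and the counts and shares used here are assumptions that show sensitivity, not a measured bias. If the recruitment and qualitative sections govern, refusals stay in, the criterion can fail, and it is not circular. The ambiguity should be settled before the rate is calculated.

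**What to change.** - In Outcome assessment, define the denominator by the clinical and language criteria only: adults with myeloma referred for consideration of transplant, clinically able to exercise, with adequate English and none of the spinal, neurological, surgical or cardiac exclusions, who were sent or offered the study.
- State that every such patient who declines for any reason, including unwillingness to exercise or to consent, counts as an eligible decliner and stays in the denominator.
- State that the unwillingness exclusions in the eligibility section are not applied when the rate is calculated. In the screening log, code the reason for refusal separately from ineligibility.
- Report recruited over all referred alongside, so that patients screened out before approach because they were presumed unwilling are also visible.

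The cost is wording and log coding. Recruitment began in June 2019, so log entries already made may need to be reclassified. The reported rate may be lower than under the looser definition.
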